## Abstract

**Introduction:**

Proximal femoral (hip) fracture is common, serious and costly. Rehabilitation may improve functional recovery but evidence of effectiveness and cost-effectiveness are lacking. An enhanced rehabilitation intervention was previously developed and a feasibility study tested the methods used for this randomised controlled trial (RCT). The objectives are to compare the effectiveness and cost-effectiveness of the enhanced rehabilitation programme following surgical repair of proximal femoral fracture in older people compared with usual care.

**Methods and analysis:**

Protocol for phase III, parallel-group, two-armed, superiority, pragmatic RCT with 1:1 allocation ratio; allocation sequence by minimisation programme with a built-in random element; secure web-based allocation concealment. The two treatments will be usual care (control) and usual care plus an enhanced rehabilitation programme (intervention). The enhanced rehabilitation will consist of a patient-held information workbook, goal setting diary and up to six additional therapy sessions. Outcome assessment and statistical analysis will be performed blind; patient and carer participants will be unblinded. Outcomes will be measured at baseline, 17 and 52 weeks’ follow-up. Primary outcome at 52 weeks will be the Nottingham Extended Activities of Daily Living scale. Secondary outcomes will measure anxiety and depression, health utility, cognitive status, hip pain intensity, falls self-efficacy, fear of falling, grip strength and physical function. Carer strain, anxiety and depression will be measured in carers. All safety events will be recorded, and serious adverse events will be assessed to determine whether they are related to the intervention and expected. Concurrent economic evaluation will be a cost-utility analysis from a health service and personal social care perspective. An embedded process evaluation will determine the mechanisms and processes that explain the implementation and impacts of the enhanced rehabilitation programme.

**Ethics and dissemination:**

National Health Service research ethics approval reference 18/NE/0300. Results will be disseminated by peer-reviewed publication.

**Trial registration number:**

ISRCTN28376407; Pre-results registered on 23 November 2018.

Strengths and limitations of this studyPragmatic phase III randomised controlled trial following phase I intervention development and phase II feasibility study.Concurrent economic evaluation with a health service and personal social care perspective.Embedded process evaluation to determine the mechanisms and processes that explain the implementation and impacts of the enhanced rehabilitation programme.Only patients with mental capacity to consent are eligible, therefore excluding a large number of potential participants lacking capacity.

## Introduction

Proximal femoral fracture, more commonly referred to as hip fracture, is a common, major health problem in old age.^1^ It is projected to increase further as the population ages.^2 3^ Mortality is high,^4 5^ and of those who survive to 1 year, 29% fail to regain their level of functioning, in terms of restrictions of activities of daily living^6^; many lose their independence. This imposes a large cost burden on society, estimated to be approximately £2.3 billion a year in the UK.^7^ The majority of costs is incurred in the community and social care setting in the 12 months following hospital discharge, which are almost four times higher than the costs of the acute hospital admission.^8^ Frail individuals are at particular risk of secondary future proximal femoral fracture, resulting in worse morbidity and mortality outcomes.^9^

The National Institute of Health and Clinical Excellence (NICE) have issued guidelines for the management of hip fracture.^10^ This includes the provision of a co-ordinated multidisciplinary rehabilitation programme starting in hospital during postoperative recovery and continuing in the community following discharge.^10^ Where possible such rehabilitation programmes should consider individual patient goals, facilitate a return to prefracture independence and provide patients and carers with written information to support the rehabilitation programme and long-term outcomes. The Hip Sprint audit reported that community rehabilitation services were inconsistent.^11^

### Rationale

There have been four relevant Cochrane systematic reviews with inconclusive results.^12–15^ These have examined different types and intensities of in-patient rehabilitation,^12^ mobilisation strategies,^13^ psychosocial functioning after hip fracture^14^ and rehabilitation for those with dementia following hip fracture surgery.^15^ Other systematic reviews have reported improved walking ability,^16^ strength and physical function,^17^ including those with mild to moderate dementia.^18^ These systematic reviews concluded that while individual components of rehabilitation programmes may aid recovery after a hip fracture, there is insufficient evidence to demonstrate clinical effectiveness or cost-effectiveness of an overall care pathway, and that further research is required.

A previous study^19^ completed the first two phases of the Medical Research Council framework for complex interventions.^20^ The first phase developed an enhanced rehabilitation intervention which, in addition to usual care, included a patient-held workbook, a goal setting diary and up to six additional home-based therapy sessions.^21^ The second phase of the study was a randomised feasibility study, which assessed the acceptability of the new rehabilitation programme and the feasibility of trial methods for a definitive phase III randomised controlled trial (RCT).^22 23^ Although this feasibility study was underpowered to assess effectiveness, the intervention showed a medium-sized improvement in the Nottingham Extended Activities of Daily Living (NEADL) scale compared with usual care (Cohen’s d 0.63). A process evaluation described the implementation of the rehabilitation programme and informed how to enhance recruitment and improve the intervention.^24^

### Risk and benefits

The enhanced rehabilitation programme demonstrated a potential improvement in activities of daily living in the feasibility study. Possible risks of rehabilitation interventions would include injury or falling when performing therapeutic exercises, which must be weighed against the risk to health of sedentary behaviour.

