### Secondary objectives

To compare the cost-effectiveness of an enhanced rehabilitation programme following surgical repair of proximal femoral fracture in older people compared with usual care at 52 weeks follow-up.To determine the effectiveness of an enhanced rehabilitation programme following surgical repair of proximal femoral fracture in older people compared with usual care, in terms of the performance of activities of daily living at 17 weeks follow-up.To determine the effectiveness of an enhanced rehabilitation package following surgical repair of proximal femoral fracture in older people compared with usual care, in terms of anxiety and depression at 17 and 52 weeks follow-up.To assess whether the enhanced rehabilitation intervention creates change in self-efficacy, hip pain, cognitive function, fear of falling and physical function as potential mediators for improving activities of daily living at 17 and 52 weeks follow-up.To assess whether the enhanced rehabilitation intervention creates change in strain, anxiety and depression in carers at 17 and 52 weeks follow-up.To determine the mechanisms and processes that explain the implementation and impacts of the enhanced rehabilitation programme and whether there are adverse effects.

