#### Enhanced rehabilitation

The main aim of the intervention is to enhance usual rehabilitation by increasing patients’ self-efficacy^25^ and increasing the amount and quality of patients’ practice of physical exercise and activities of daily living to improve functional outcomes at follow-up. Self-efficacy will be enhanced by means of a patient-held information workbook and a goal setting diary. The workbook will include:

Information about what has happened to them and what to expect from their recovery.Information about NHS, council and voluntary sector services including falls’ prevention programmes.How to manage their recovery, set goals and monitor progress of their rehabilitation; reduce fear of falling.

In addition to whatever community-based rehabilitation is provided as part of usual care, we will provide up to six additional therapy sessions, once patients are discharged home. These can be delivered by physiotherapists, occupational therapists or their assistants, who have been trained to deliver these extra sessions alongside the workbook, using the diary to set goals and monitor progress. The therapists will tailor these extra sessions, so that the total number of sessions used, the time scale for their delivery and the sessions’ content will vary between patients according to need but may include the practice of specific exercises and activities of daily living. Throughout the running of this trial, therapists will receive on-going support via emails, newsletters and refresher events.

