### Outcomes

Patient participants will complete outcome measures at baseline, 17 and 52 weeks administered by a research assistant blinded to participant allocation. Follow-up assessments will be completed within participants’ homes (tables 1 and 2). The primary outcome will be the difference in NEADL scale^26 27^ at 52-week follow-up, between the usual rehabilitation arm and the enhanced rehabilitation arm. At baseline, the patient will be asked to recall the 4 weeks prior to hip fracture and not 4 weeks prior to completing this questionnaire. Secondary outcomes will include the Hospital Anxiety and Depression Scale (HADS),^28^ economic measures will be EuroQol, EQ-5D-3L^29^ and Client Service Receipt Inventory.^30^ A reduced version of this will be used at baseline to reduce participant burden as they recover from hip fracture surgery. Potential mediators of outcome will include a Visual Analogue Scale (VAS) for hip pain intensity,^31^ Falls Efficacy Scale—International (self-efficacy)^32 33^ and Visual Analogue Scale—Fear of Falling (VASFoF).^34^

**Table 1 T1:** Outcome measures

Patient completed measures—primary	Description	Range
Nottingham Extended Activities of Daily Living scale^26 27^	Activities of daily living (mobility, kitchen, domestic, leisure) with higher score indicating greater independence	(0–66)

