**Patient completed economic measures**		
EuroQol EQ-5D-3L^29^	Health utility index with five dimensions (mobility, self-care, usual activities, pain/discomfort, anxiety/depression) and three levels to give health states converted to a utility weight. Also Visual Analogue Scale (VAS) for health state today	Health utility weight from 0 (death) to 1.0 (perfect health) also with negative values VAS (0–100)
Client Service Receipt Inventory 30	Use of health and social care services	According to activity
**Patient completed process measures (potential mediators of outcomes**)		
Visual Analogue Scale (VAS) for hip pain intensity^31^	VAS of current hip pain intensity	(0–10 cm)
Falls Efficacy Scale— International (self-efficacy)^32 33^	How concerned a patient is about falling when performing 16 activities of daily living both inside and outside of the home, rated from 1 (not at all concerned) to 4 (very concerned)	(16–64)
VAS-Fear of Falling^34^	VAS with higher scores indicating greater fear of falling	(0–10 cm)

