### Ethics and dissemination

NHS research ethics approval was obtained from North East—Tyne & Wear South Research Ethics Committee, reference 18/NE/0300. The current protocol is V.4.0 (11 December 2019). A Trial Steering Committee is providing overall supervision and an Independent Data Safety and Monitoring Committee is responsible for reviewing and assessing recruitment, interim monitoring of safety and effectiveness, trial conduct and external data.

All safety events will be recorded by researchers when they are made aware of the event by the patient, carer, the treating clinicians or therapists. Adverse event reports and serious adverse events (SAEs) not related to the intervention will be entered on to the remote data entry system. Each SAE will be assessed by the relevant principal investigator (PI) to determine whether it is related to the intervention. A related SAE will be assessed by the CI to determine whether it is expected. If the SAE is related and unexpected, it will be reported to the Research Ethics Committee and sponsor in an expedited manner.

Reporting of the trial will be consistent with the Consolidated Standards of Reporting Trials 2010 Statement (patient-reported outcomes and non-pharmacological interventions).^53^ We will submit the final report to a peer-reviewed academic journal, according to our publication strategy and authorship policy. Research data will be available for secondary analysis on reasonable request.

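### Falling is a named risk, but falls reach the data only when researchers hear of them, by routes that differ between arms; two identical questions in both arms would fix this

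*Protocol article*

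**What the plan says.** All references are to the protocol article.

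- **Risk and benefits** gives the possible harms: "Possible risks of rehabilitation interventions would include injury or falling when performing therapeutic exercises".
- **Secondary objectives** ends with an objective to "explain the implementation and impacts of the enhanced rehabilitation programme and whether there are adverse effects".
- **Enhanced rehabilitation** describes a programme that works by "increasing the amount and quality of patients’ practice of physical exercise and activities of daily living". Its workbook covers how to "set goals and monitor progress of their rehabilitation; reduce fear of falling".
- **Outcomes, Table 1** lists two instruments on falling, both classed as potential mediators. One is the Falls Efficacy Scale – International, described as "How concerned a patient is about falling when performing 16 activities of daily living both inside and outside of the home". The other is a visual analogue scale for fear of falling. Neither counts falls, and Tables 1 and 2 contain no fall or fall-injury item.
- **Table 2** ticks monitoring of adverse events and of serious adverse events (SAEs) at 17 weeks, at the interviews and at 52 weeks. It also ticks them in the trial-intervention column, which carries a footnote limiting it to patients randomised to the intervention.
- **Ethics and dissemination** says researchers record a safety event once the patient, carer, treating clinician or therapist has brought it to their notice. It adds: "Each SAE will be assessed by the relevant principal investigator (PI) to determine whether it is related to the intervention". Adverse event reports and SAEs judged unrelated are also entered in the data system.
- **Blinding** states that patients and clinicians cannot be blinded.

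**The concern.** The programme aims to increase activity and to lower fear of falling. Greater activity with less caution could plausibly change how often patients fall, in either direction. The fear side is measured with two instruments, in the same way in both arms. The event side depends on what comes to a researcher's attention, and the routes for that are not the same in the two arms.

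A difference in recorded falls would then be hard to read. An apparent excess under enhanced rehabilitation could be better detection, and a true excess could be explained away as better detection. A fall in fear-of-falling scores would have no equally ascertained fall count beside it. The objective on adverse effects would lose much of the protection that randomisation should give it.

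**Working it through.** **Routes of capture, side by side**

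| Feature | Usual care | Enhanced rehabilitation |
|---|---|---|
| Event monitoring ticked at 17 and 52 weeks (Table 2) | yes | yes |
| Event monitoring ticked in the intervention column (Table 2 and its footnote) | no | yes |
| Extra therapist contacts, therapists being a reporting source | none | as many as six |
| Patients and clinicians know the allocation | yes | yes |
| Events entered whatever the relatedness judgement | yes | yes |

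The last row makes a comparison by arm possible. Rows two to four make unequal capture likely.

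**The plan's own sample size.** The inputs are a difference of 2.4, SD 10, R² 0.52, alpha 5% (taken as two-sided), power 90% and retention 79%.

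- Residual SD = 10 × √(1 − 0.52) = 6.93.
- n per arm = 2 × (1.960 + 1.282)² × 48 / 2.4² = 175.1, so 176 per arm and 352 in total.
- 352 / 0.79 = 445.6, so 446 in total and 223 per arm.

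Both stated totals (352 and 446) reproduce. They supply the arm sizes below.

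**Effect of unequal capture.** The documents give no fall rate and no capture rate, so every rate here is an assumption. Let 40% of patients truly fall in each arm, and let 50% of control fallers be captured, so that recorded control fallers are 0.40 × 0.50 = 20%. Power uses the normal approximation Φ[(d − 1.96 × SE₀)/SE₁], with a pooled SE₀ and an unpooled SE₁.

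| Capture, intervention arm | Recorded fallers, intervention v control | Risk ratio | Declared significant at 223 per arm |
|---|---|---|---|
| 50% | 20% v 20% | 1.0 | no bias |
| 60% | 24% v 20% | 1.2 | 17% |
| 70% | 28% v 20% | 1.4 | 51% |
| 80% | 32% v 20% | 1.6 | 83% |
| 90% | 36% v 20% | 1.8 | 97% |

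For the 70% row, SE₀ = √(0.24 × 0.76 × 2/223) = 0.0405 and SE₁ = √[(0.20 × 0.80 + 0.28 × 0.72)/223] = 0.0403. Then Φ[(0.08 − 1.96 × 0.0405)/0.0403] ≈ 0.51. The arm size is 223 because safety events are recorded for everyone randomised.

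The same recorded 28% v 20% would also arise from a real excess with equal capture: 56% v 40% truly falling, half captured in each arm (0.56 × 0.50 = 0.28). The recorded data could not separate the two cases.

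**What identical questions would give.** The answers come from patients assessed at follow-up, so the arm size is the 176 planned completers. With an assumed 40% of controls falling:

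- 50% v 40%: SE₀ = √(0.45 × 0.55 × 2/176) = 0.0530 and SE₁ = √[(0.24 + 0.25)/176] = 0.0528. Power = Φ[(0.10 − 1.96 × 0.0530)/0.0528] ≈ 47%.
- 55% v 40%: power ≈ 81%.
- 95% CI half-width = 1.96 × √(2 × 0.40 × 0.60/176) = 0.102, about 10 points.
- Over assumed control rates of 20% to 50%, the smallest increase detectable with 80% power is 13.2 to 14.9 points.

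**The case against.** A reader might infer that the trial does not record falls at all, that it could never tell regained confidence from more falls, or that the adverse-effects objective rests on the principal investigator's view of relatedness, which can implicate only the intervention arm. The documents do not support any of these. All safety events are to be recorded, monitoring is ticked at 17 and 52 weeks for both arms, and events judged unrelated are still entered. Relatedness and expectedness are described as the path to expedited reporting, not as the basis of the objective. A reported fall judged unrelated is therefore not lost.

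It is also fair to say that the article condenses a longer protocol. Event definitions, the content of the event form, any prompt about falls and the reports to the monitoring committee may sit there, and their absence here is no fault. The named risk is falling or injury during therapeutic exercises, which is narrower than all falls over a year. Therapists also record the length and content of each extra session and complete critical incident reports. The footnoted column in Table 2 may mark only the treatment period.

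What remains is what the article does state. Its outcome table and schedule go instrument by instrument and contain no fall count. Its capture rule depends on unblinded people bringing events to notice, with more therapist contact in one arm. The session forms and incident reports add to that imbalance, because they concern the extra sessions.

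**Conclusion.** The point holds as a cheap improvement, not as an error that invalidates the plan. A named risk tied to a stated objective has no listed measure asked in the same way in both arms, while the fear that the programme aims to lower has two fall-related instruments. A comparison of recorded falls by arm is possible but open to ascertainment bias. If capture were 50% in control and 60% to 90% in the intervention arm, with equal true rates of 40%, the spurious risk ratio would run from 1.2 to 1.8. With equal capture there would be no bias. These rates are assumptions. The documents fix only the routes of capture, so the likely direction is clearer than the size.

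**What to change.** At the existing 17- and 52-week assessments, including the telephone and postal versions, ask both arms the same two questions: the number of falls since the last assessment, and whether any fall caused a fracture or needed medical care. Compare the answers by randomised arm regardless of relatedness, and present them beside the fear-of-falling results. Keep relatedness judgements for the reporting purpose already described.

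The cost is two questions at two assessments and one table. The downsides are:

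- a slightly longer questionnaire;
- under-counting through recall, which may differ between arms because patients know their allocation;
- incomplete early counts for the 96 patients recruited at submission, though 446 − 96 = 350 of the planned sample were still to come;
- moderate precision, so the result should be reported as an estimate with its confidence interval, and a non-significant difference should not be read as evidence of safety.

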### Primary objective

To determine the effectiveness of an enhanced rehabilitation programme following surgical repair of proximal femoral fracture in older people compared with usual care, in terms of the performance of activities of daily living at 52 weeks follow-up.

### Secondary objectives

To compare the cost-effectiveness of an enhanced rehabilitation programme following surgical repair of proximal femoral fracture in older people compared with usual care at 52 weeks follow-up.To determine the effectiveness of an enhanced rehabilitation programme following surgical repair of proximal femoral fracture in older people compared with usual care, in terms of the performance of activities of daily living at 17 weeks follow-up.To determine the effectiveness of an enhanced rehabilitation package following surgical repair of proximal femoral fracture in older people compared with usual care, in terms of anxiety and depression at 17 and 52 weeks follow-up.To assess whether the enhanced rehabilitation intervention creates change in self-efficacy, hip pain, cognitive function, fear of falling and physical function as potential mediators for improving activities of daily living at 17 and 52 weeks follow-up.To assess whether the enhanced rehabilitation intervention creates change in strain, anxiety and depression in carers at 17 and 52 weeks follow-up.To determine the mechanisms and processes that explain the implementation and impacts of the enhanced rehabilitation programme and whether there are adverse effects.

## Methods and analysis

### Trial design

This is a pragmatic, multisite, parallel-group, two-armed, superiority RCT with 1:1 allocation ratio and an internal pilot phase (figure 1). Outcome assessment and statistical analysis will be blinded; patient and carer participants and clinicians will be unblinded. A concurrent economic evaluation will be a cost-utility analysis from a health service and personal social care perspective. An embedded process evaluation will examine the mechanisms and processes that explain the implementation and impacts of the enhanced rehabilitation programme. The RCT was registered on 23 November 2018. Trial registration data can be found in online supplemental appendix 1.

10.1136/bmjopen-2020-039791.supp1Supplementary data

